## Measures

### Primary outcome measures

#### Child symptoms

##### Trauma symptoms

*Trauma Symptom Checklist for Younger Children* [50]. The TSCYC is a parent-reported questionnaire for children (3–12 years) measuring posttraumatic stress symptoms on a 4-point Likert scale, ranging from ‘not at all’ (1) to ‘very often’ (4). It consists of 90 items and 11 scales: two scales to assess the validity of the parent’s answers (response level and atypical response), eight clinical scales (anxiety, depression, aggression, PTSS-intrusion, PTSS-avoidance, PTSS-arousal, dissociation and sexual concerns) and a total PTSS score. This total score will be used in analyses. This clinical total PTS scale showed good reliability within a sample of maltreated children in the United States (Cronbach’s α = 0.81–0.91) and in the Netherlands (Cronbach’s α = 0.79–0.91) [51].

*Trauma Symptom Checklist for Children* [52]; Dutch translation: *Trauma Symptoom Controle Lijst voor Kinderen* [53]. This is a questionnaire to assess self-reported posttraumatic stress symptoms at children (8–12 years). It consists of 54 items clustering in 8 scales: two validity scales (underresponse, hyperresponse) and six clinical scales (anxiety, depression, post-traumatic stress disorder, dissociation, anger and sexual concerns). The response categories are the same as in the Trauma Symptom Checklist for Younger Children and reliability was high for the clinical total PTS score, with a Cronbach alpha’s ranging from 0.78 to 0.86 in a sample of sexually abused children [50]. In a sample of maltreated children in the United States the Trauma Symptom Checklist for Children showed discriminant and convergent validity with the Trauma Symptom Checklist for Younger Children [54], and in the Netherlands the Trauma Symptom Checklist for Children showed convergent and criterion validity with other behavioral questionnaires (CBCL, TRF, YSR, CDI) [55].

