### Parental availability

*Security in the Family System:* The Security in the Family System scale [87] will be used to assess how much children perceive their families as a reliable source of protection, stability, and support. The subscale ‘Secure’ will be used, which assesses a secure pattern of emotional security. Children indicate the extent to which they agree with 7 statements using a four-point scale ranging from ‘Complete disagree’(1) to ‘Complete agree’(4). Psychometric properties of this security subscale are good, Cronbach’s α = 0.85 and test-retest reliability = 0.82 [87].

*The cognitive emotion regulation questionnaire* [88] is a self-report measure developed in the Netherlands that assesses cognitive coping-styles of adults and adolescents aged 12 years and older. Two subscales of the cognitive emotion regulation questionnaire are included in this study: rumination and catastrophizing*.* Each subscale has 4 items, and has good internal consistency (α = 0.83 for rumination and α = 0.79 for catastrophizing [88]. The parent rates how often he or she uses a certain coping style on a 5-point scale ranging from ‘(almost) never’(1) to ‘(almost) always’(5). We use two versions of the questionnaire, one with the original questions and one version adapted for this study. The adapted version asks parents to report on how they cope with the traumatic events that happened to their children.

*Emotional Awareness: The Emotional Awareness Questionnaire* [65] is described in more detail above. For parents, we will include two subscales: “Not Hiding Emotions” and “Other’s Emotions”. We changed the items belonging to the Other’s Emotions subscale to enquire about children, not friends.

*Daily Psychological Availability Scale* [89]. To assess parental availability for the child we will use eight adapted items of the Daily Psychological Availability Scale. Items were measured using 7-point scales from 1 (totally disagree) to 7 (totally agree). Cronbach’s α was 0.78 for both fathers and mothers [89]. A higher score on this scale represents more psychological availability for the child.

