### Secondary objectives

To investigate associated changes between: child symptoms, on the one hand, and 1) child responses (i.e., child emotional, behavioral, and cognitive responses), 2) parental availability and 3) parent-child interaction on the other, we will use the stepwise procedure in multivariate regression analyses with a maximum of 4 tested predictors. With a sample size of 100, alpha of .05 and medium effect size (f^2^ = .15), we will achieve a power of .87 in analyses with 4 individual predictors. We will use latent variables for child responses, parental availability and parent-child interaction.

We will also use multivariate regression analyses to study the fourth goal, namely which mechanisms explain how the two components added to the TF-CBT-based Horizon treatment contribute to the effectiveness of TF-CBT-based Horizon treatment. We will follow Holmbeck’s recommendations [120] for these mediational analyses and will test the robustness of our results by using the bootstrapping method. These analyses will allow us to determine whether the parent-child interaction variables and parental availability partly or fully mediate the effects of each parental component on child symptoms. Specifically, we will test whether, as predicted, the preparatory program leads to increased parental availability and whether the parent-child interaction sessions lead to improved parenting behavior. Also, we will explore whether these changes lead to a reduction in symptoms. Because at least partial mediation is assumed, a small to medium effect size is chosen (f^2^ = .10). Two models are tested. A first model with component 1 (preparatory parent program) and parent availability as independent variables. And a second model with component 2 (parent-child interaction sessions) and parent-child interaction as independent variables. With a sample size of 100, alpha of .05 and medium effect size (f^2^ = .10), we will achieve a power of .80 if 2 predictors are tested in the regression.

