## Discussion

This study aims to bridge the gap between clinical practice and scientific research [122]. It examines mechanisms underlying change in psychotherapy for children exposed to IPV, explains how components of therapy work, and identifies moderators of treatment effects. The results, which are obtained in a RCT-study in collaboration with different trauma centers, will provide unique insights to improve clinical decision-making.

First, the RCT-design provides the best possible controls for evaluating the efficacy of psychiatric treatment. Rather than using a waiting list control group, the study zooms in on two parental components and mechanisms of change not yet investigated. All children receive TF-CBT, an established treatment for traumatized children [17], including psycho-education, parenting skills, relaxation, affective expression and modulation, trauma narrative, and cognitive coping and processing.

Second, the study focuses on the efficacy of two IPV-related parental components added to TF-CBT. To date, research on effective components of treatment for post-traumatic stress disorder focused on trauma-oriented components [123]. Research on effective components of TF-CBT focused on the trauma-narrative [124], on treatment lengths [124], and on inclusion of parents [125]. Nevertheless TF-CBT is less effective for children exposed to IPV than for children otherwise traumatized [9]. Children exposed to IPV are not only traumatized, but IPV also directly and indirectly affects their emotional, cognitive and behavioral responses. By considering this complexity this study provides important insights into the efficacy of specific IPV-related parental components. These insights are crucial to improve the treatment and maximize its effects for this specific target group [124].

The use of multiple informants (parent, child and teacher) and independent observations and interviews are likely to diminish reporting-bias. To pinpoint underlying mechanisms and assess the longer-term consequences of the intervention multiple data collections takes place, including a follow-up at 6 months after the end of treatment. This converging evidence will allow us to establish the reliability and validity of the collected information considerably.

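### The mechanism models do not separate informants, so one parent's reporting can inflate the mediator-to-symptom path; the plan's safeguards reduce this bias but do not reliably remove it

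*Protocol article*

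**What the plan says.** The statistical section on Secondary objectives defines two mediation models by construct: "A first model with component 1 (preparatory parent program) and parent availability as independent variables" and "And a second model with component 2 (parent-child interaction sessions) and parent-child interaction as independent variables". It adds: "We will use latent variables for child responses, parental availability and parent-child interaction". No informant, informant factor or baseline score is named for these models. Their power statement reads "With a sample size of 100, alpha of .05 and medium effect size (f^2^ = .10" and "we will achieve a power of .80 if 2 predictors are tested in the regression".

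The informants have to be read from the Measures sections:

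- **Availability scales (Parental availability).** Family security is child-reported. Coping ("The parent rates how often he or she uses a certain coping style on a 5-point scale"), emotional awareness and daily psychological availability are parent-reported. The same section adds two parent-child concordance measures: the trauma-reaction inventory at sessions 1, 9 and 15, and the session 6 comparison.
- **Parent-child variables.** Attachment security and trust beliefs are child-reported. Parenting, closeness and time together have both informants. Capitalization, protective factors and household chaos are parent-reported.
- **Symptoms (Primary outcome measures).** "The TSCYC is a parent-reported questionnaire for children"; the TSCC is self-report at 8 to 12 years; the CBCL is parent-reported and the TRF teacher-reported. Teachers receive a questionnaire at every assessment.
- **Interview and observational tasks (Control measures).** T1 only.

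The Discussion states: "The use of multiple informants (parent, child and teacher) and independent observations and interviews are likely to diminish reporting-bias".

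**The concern.** A distressed or self-critical parent may rate both their own availability and the child's state unfavourably. That makes the two scores correlate even if availability has no effect on symptoms. Randomizing the component protects its effect on the mediator. It does not protect the mediator-to-symptom path, which is observational within arms.

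The Discussion relies on multiple informants and independent observation against reporting bias, but no analysis section carries this into the mechanism models. The interview and observational tasks cannot help as post-treatment mediators, because they are done only at T1. At stake is the conclusion for goals 3 and 4: that availability or parenting explains symptom change.

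**Working it through.** **The plan's own figures.** Omnibus F test, λ = f²·N, df = (u, N − u − 1), alpha .05, N = 100:

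- u = 2, f² = .10: .803 (stated .80)
- u = 4, f² = .15: .874 (stated .87)
- u = 5, f² = .15: .843 (stated .84)

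All reproduce. The issue is bias, not power.

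**Model for the check.** N = 100, 50 per level of the component, independent data. The true effect of mediator and component on symptoms is zero. Let S be a stable parent style, s the share of each parent-reported score due to it, and T the component:

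M = √s·S + √(1 − s)·m + a·T; Y = −√s·S + √(1 − s)·y; m and y independent.

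Given T, the correlation of M and Y is −s. Assumptions not in the documents: s = .10, .20, .30; a = 0, 0.5 or 0.8 SD. Mediation is declared when the component-to-mediator path (a) and the mediator-to-symptom path (b) are both significant at .05.

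**Hand check of the unprotected case.**

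- b path: noncentrality = s·√97/√(1 − s²) = 0.99, 2.01, 3.10. The critical value is 1.985, so b is falsely significant in about 16%, 51%, 87%.
- a path at 0.5 SD: noncentrality = 0.5·√25 = 2.5, power about 70%.
- Both: about .70 × (.16, .51, .87) = 11%, 36%, 61%.
- With a = 0 the a path is significant in 5%: .05 × (.16, .51, .87) = 1%, 3%, 4%.

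**Simulated false mediation, %.** Where 4,000 trials were run per setting, the simulation error is at most √(.25/4000) = 0.8 points.

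| Setting | s = .10 | .20 | .30 |
|---|---|---|---|
| Same parent, a = 0.5, no safeguard | 12 | 36 | 61 |
| Same parent, a = 0.8, no safeguard | 17 | 52 | 83 |
| Same parent, a = 0 | 1 | 3 | 4 |
| a = 0, but component shifts parents' reporting style by 0.5 SD | 2 | 10 | 24 |
| a = 0.5, half the style variance in the mediator (mixed informants) | 8 | 19 | 41 |
| a = 0.5, covariate capturing half the style variance | 6 | 16 | 32 |
| a = 0.5, that covariate and a mixed-informant mediator | 4 | 9 | 16 |
| a = 0.5, T1 mediator and T1 symptoms in the model, stable style | 5 | 7 | 10 |
| Outcome from another informant, a = 0.5 or 0.8 | 3–5 | 3–5 | 3–5 |

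The covariate row can be checked by hand. A covariate that captures half of S leaves a partial correlation of .5s/(1 − .5s) = .053, .111, .176. The b path is then falsely significant in about 8%, 19%, 41%. The a path has power of about 72%, 74%, 77%, and the products are about 6%, 14%, 31%.

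In change scores the term √s·S subtracts out exactly, provided style is the same at both times and the component does not alter it.

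**Cost of the child-report route.** If ages 4 to 12 were evenly filled, 100 × 5/9 ≈ 56 children could complete the TSCC; 50 is a second assumption. With u = 2 and f² = .10, power is .53 at N = 56 and .48 at N = 50.

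**The case against.** The case on the other side has four parts.

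- **The constructs are not parent-only.** The availability section includes two measures that compare parent and child directly, and the parent-child list includes several child reports. The primary outcomes include the TSCC and TRF. A reader might infer that the plan prescribes same-parent pairing. It does not; it leaves pairing open. This dilutes the bias, but 8/19/41% remains if half the style variance enters the mediator.
- **Parental psychopathology is controlled.** The general analysis section says so, and this is the most obvious source of a negative reporting style. The covariate is itself parent self-report and will capture style only in part. Even at half, 6/16/32% remains.
- **Goal 3 concerns associated changes, and the cross-lagged models condition on earlier waves.** A stable style largely cancels in change scores, so cross-sectional false-positive rates should not be read as the rate for goal 3. But the two mediation models name no baseline or change score, and distress that shifts during treatment would not cancel. Bootstrapping addresses sampling error, not this bias. The cross-lagged analysis is exploratory and names no informant either.
- **Informant handling may be left to a fuller plan.** This is fair for loadings and method factors. It is weaker here because the article claims protection from multiple informants while defining models that need not use them.

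A reader might also infer that reporting style alone manufactures mediation. It does not: with no movement of the reported mediator the rate is 1/3/4% and the mean indirect effect is zero. The protocol does, however, predict that movement.

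**Conclusion.** The concern holds in limited form. The goal 3 and 4 models let one parent supply much of both the mediator and the symptom score. If the component moves the reported mediator, shared reporting can yield false mediation.

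Under style shares of 10 to 30% and a 0.5 SD shift, the rate is about 12 to 60% with no safeguards. It is about 4 to 16% with a good psychopathology covariate and a mixed-informant mediator, against a nominal 5% or less. The second range is the fairer description of the plan if its covariate control and child reports are both carried into these models. The style shares, the shift, the covariate's strength and independence of observations are all assumptions.

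The stated power figures are correct. A reader might extend the point to the primary comparison of components, but this argument concerns only the mediator-to-symptom path. It is worth correcting because mechanisms of change are a main claim of the trial and the correction needs no new data.

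**What to change.** In the statistical section on Secondary objectives:

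1. Add the T1 mediator and the T1 symptom score to each mechanism model.
2. For internalizing and externalizing problems, report parent-reported mediators with TRF outcomes, and child-reported mediators with parent- or teacher-reported outcomes, alongside the same-parent models.
3. For trauma symptoms, report the TSCC pairing at ages 8 to 12 as a sensitivity analysis, and state that a mechanism seen only in same-parent data may reflect shared reporting.

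Cost: extra analyses, and smaller, less precise models because of teacher non-response (no rate is given) and the TSCC age limit. Requiring agreement across informants for every mechanism claim would go too far. The TRF is planned for internalizing and externalizing problems, not trauma symptoms, so a trauma claim would then rest on a subset with power near .5 under the age assumptions above.

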### Statistical analyses and sample size calculation

All variables are measured on at least an ordinal scale. All scale scores will be examined for normality. Should we observe deviations, steps will be taken to ensure optimal estimation of parameters in our analyses. The proposed study includes a nested structure, because individuals are treated within groups. Following the recommendations by Peugh [118], we will calculate design effects to assess group-level dependency and examine whether multi-level modeling is required. To ensure comparability of the randomized conditions, we will control for duration and severity of the IPV [45], parental psychopathology [46], and new incidents of IPV. Power calculations were performed using the program G*power 3 [119], assuming that individual-level effects can be treated as independent data. We determine required sample size to be 100 parent-child dyads, achieving statistical power of at least .80 for the primary and secondary objectives, as described in more detail in the following paragraphs. We will test for the randomness of missing data. If this is the case we will use multiple imputation.

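### The .80 power quoted for the mediation goal is the power of an overall two-predictor F test, not of the indirect effect

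*Protocol article*

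**What the plan says.** In the protocol article, the analysis section headed Secondary objectives says the fourth-goal analyses will determine whether the parent-child interaction variables and parental availability "partly or fully mediate the effects of each parental component on child symptoms". Bootstrapping is named as a check on robustness. The same paragraph says it will test whether "the preparatory program leads to increased parental availability and whether the parent-child interaction sessions lead to improved parenting behavior".

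Two models are listed: "A first model with component 1 (preparatory parent program) and parent availability as independent variables", and "And a second model with component 2 (parent-child interaction sessions) and parent-child interaction as independent variables". The effect size is justified this way: "Because at least partial mediation is assumed, a small to medium effect size is chosen (f^2^ = .10"). One power figure follows for the goal: "we will achieve a power of .80 if 2 predictors are tested in the regression".

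The section Statistical analyses and sample size calculation sums up the choice of 100 dyads as "achieving statistical power of at least .80 for the primary and secondary objectives". It states that the calculations were done in G*Power 3 and treat individual-level effects as independent. No effect size or power is given for the component-to-mediator path or for the indirect effect.

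**The concern.** Mediation is a claim about two links in a chain: the component changes the mediator (path a), and the mediator, with the component held fixed, is related to symptoms (path b). The indirect effect is the product of the two, and it is zero if either is zero. The power statement concerns one regression of symptoms on component and mediator. That regression contains path b and the direct effect but says nothing about path a. It can be significant purely because availability and symptoms are correlated, whether or not the preparatory program affects availability.

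So a figure for one test is attached to a different question, and the summary sentence carries it forward as power for the secondary objectives. If readers take .80 at face value, they will give a non-significant mediation result more weight against the mechanism than the design can bear.

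**Working it through.** **Inputs from the article.** N = 100, alpha = .05, f² = .10, two predictors (component and mediator), independent observations, 2 × 2 factorial.

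**Step 1: reproduce the .80.** Overall F test of R² = 0 with u = 2 predictors:

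- noncentrality λ = f² × N = .10 × 100 = 10
- df = 2 and 100 − 2 − 1 = 97
- critical F(.95; 2, 97) = 3.09
- power = P(noncentral F > 3.09) = .803

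The same convention also returns the article's other two figures: five predictors at f² = .15 give .843 (stated .84), and four give .874 (stated .87). A test of one coefficient in the two-predictor model would give .879, which does not match. The .80 is therefore the overall F test, and it is computed correctly.

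**Step 2: set up the mediation model.** In standardised form, with the component X split 50/50:

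- M = aX + e₁
- Y = c′X + bM + e₂
- overall R² = f²/(1 + f²) = .10/1.10 = .0909
- b solves b² + 2abc′ + c′² = .0909
- component-to-mediator difference d = 2a/√(1 − a²)

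Example: a = .25 and c′ = .10 give b² + .05b − .0809 = 0, so b = .26, and d = .50/√.9375 = .52.

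The sizes of a and c′ and the 50/50 split are assumptions; the article states none of them. The indirect effect counts as detected when the a and b tests both give p < .05 (joint significance).

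**Step 3: remove mediation altogether.** With a = 0, simulation at N = 100 gives:

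- overall F test rejects: about .79
- joint significance rejects: about .04

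The quoted power is thus reached almost in full when the true indirect effect is zero.

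**Step 4: indirect-effect power under the plan's own f² and N** (simulation, good to about ±.01):

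| a | d | c′ = 0 | c′ = .10 | c′ = .15 |
|---|---|---|---|---|
| .15 | .30 | .27 | .25 | .22 |
| .20 | .41 | .45 | .39 | .33 |
| .25 | .52 | .61 | .53 | .44 |
| .30 | .63 | .73 | .62 | .50 |
| .40 | .87 | .80 | .63 | .49 |

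The overall F test stays at about .79–.80 in every cell.

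**Step 5: the first link alone.** A two-sided t test of 50 against 50 on the mediator has power .32 at d = .30, .70 at d = .50 and .88 at d = .63. For smaller component effects, the first link by itself keeps mediation power below .80.

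**Step 6: sensitivity to the test and to how f² is assigned.**

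- At d = .50, with direct effects of 0, .2 and .3 in residual-SD units (about 0, .10 and .14 standardised), the percentile bootstrap gives .57, .55 and .45. The bias-corrected bootstrap gives .67, .66 and .58.
- At d = .80 with no direct effect, the bias-corrected bootstrap gives about .85.
- If f² = .10 is assigned to the b path alone, with no direct effect, joint significance gives .61 at d = .50, .76 at d = .63 and .84 at d = .80.

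**The case against.** The strongest reply is that nothing is miscalculated and the article says what it computed: the .80 is conditioned on two predictors being tested in the regression, and both models are spelled out. It can be added that the aim is secondary. The text tests, as a prediction, whether each component changes its mediator, and only explores whether those changes lead to fewer symptoms. The predicted first step has power .88 if d = .63. If f² = .10 is applied to each path with no direct effect, indirect-effect power is .76, close to .80.

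Part of this stands. There is no arithmetic error, and a careful reader can see that a regression is meant. It does not rescue the claim. The figure is the only one given for a goal that the same paragraph says will determine partial or full mediation, and the summary sentence extends .80 to the secondary objectives without exception. The .76 also assumes no direct effect, while the stated reason for choosing f² = .10 is that mediation is at least partial, which allows for one.

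Several stronger readings are tempting, and the documents do not support them:

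- **That the trial has only an even chance of detecting mediation.** This needs a particular d and direct effect, and the article gives neither.
- **That a medium component effect gives a particular power.** The article calls f² = .15 medium, and calls f² = .10 small to medium in one sentence and medium in another. For a 50/50 contrast d = 2√f², so these are d = .77 and d = .63. Equating medium with d of about .5 would be the reader's own choice.
- **That power with partial mediation has a fixed ceiling in the low .60s.** With a standardised direct effect of .10, joint significance reaches about .65 at d = .75 to .80, and a bias-corrected bootstrap goes higher.
- **That the investigators will treat a null result as disproof.** The article states no rule for interpreting a null mediation result.

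Clustering within therapy groups and within families is a separate matter and is not counted here.

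**Conclusion.** The point holds as a mislabelled power claim. The .80 belongs to the overall two-predictor F test and stays near .80 when the component has no effect on the mediator. It is not the power for the mediation goal, and the claim of at least .80 for the secondary objectives is unsupported there. This conclusion depends on no assumed path size; it follows from steps 1 and 3.

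The size of the shortfall does depend on assumptions. With overall f² = .10, a 50/50 split, independent dyads, joint significance and a standardised direct effect from 0 to .15, power is about .22–.27 at d = .30, .44–.61 at d = .52, .50–.73 at d = .63 and .49–.80 at d = .87. Other path sizes, a bias-corrected bootstrap, or assigning f² = .10 to the b path alone would move these figures, in some cases above .80. They illustrate the gap and do not bound it. The sample size and the primary analysis are unaffected.

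**What to change.** - In Statistical analyses and sample size calculation, and in the analysis section Secondary objectives, state that .80 refers to the overall two-predictor regression.
- Withdraw the .80 claim for mediation, or replace it with indirect-effect power for declared a, b and direct-effect values under the declared bootstrap test. One example of such a statement is about .53 by joint significance at d = .52, b = .26 and a standardised direct effect of .10. The bootstrap figure should be computed for the variant actually chosen, because percentile and bias-corrected versions differ by about .10 or more at d = .50.
- Report each indirect effect with its bootstrap interval as an estimate, and say in advance that a non-significant result will not be taken as absence of the mechanism.

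The cost is a change of wording and a less favourable stated figure. No change to sample size, allocation or data collection is needed.
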